### Outcomes

The primary outcome of this study is the rate of achievement of optimal glycemic control within 6 weeks, which is defined as FPG <95 mg/dL or 2-hour PPG <120 mg/dL in >80% of total SMBG test results.

The secondary outcomes include time to achievement of optimal glycemic control, rate of insulin therapy, and rate of side effects. Treatment failure is defined as inadequate glycemic control after 2000 mg of metformin PR. In this situation, insulin therapy is initiated. Side effects will be evaluated by interviewing the participants at each visit and by additional contact via a telephone call, SMS, or other online platforms.

The participant timeline is displayed in Figure 1.

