## Introduction

Gestational diabetes mellitus (GDM) is one of the most common complications in pregnancy; it can lead to various adverse maternal and neonatal outcomes, including preeclampsia, cesarean section, large-for-gestational-age infants, macrosomia, birth injuries, shoulder dystocia, and neonatal hypoglycemia [1-3]. Optimal glycemic control (fasting plasma glucose [FPG] of <95 mg/dL and 2-h postprandial glucose, 2-h PPG of <120 mg/dL) is key to reducing the risk of developing adverse pregnancy outcomes [1-3].

In general, nutritional therapy, behavioral modification (including physical activity and exercise), and glucose monitoring and control are the main interventions to provide to all women with GDM to achieve glycemic targets. However, if glycemic control is inadequate, additional medications are needed. Insulin has long been used as the first-line medication in GDM. Nevertheless, a large body of evidence has consistently shown that metformin is also an effective medication for glycemic control in GDM. It has been reported that metformin helps in better glycemic control, better control of weight gain, reduction in adverse pregnancy outcomes, and reduction in insulin need and dosage requirement [4-14]. In addition, metformin has been reported to be safe to use during pregnancy [6,15-19] and appears to be more cost-effective compared to insulin in the treatment of GDM [20]. Currently, many international authorities recommend the use of metformin in women with GDM [1,21,22].

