### GDM Diagnosis and Management

According to current institutional guidelines, GDM screening and diagnosis are offered to all pregnant women at the first antenatal care visit and repeated at 24 to 28 weeks of gestation if the initial screening results are normal. A 50-g glucose challenge test is used as a screening test with a 140 mg/dL cutoff value, and a 100-g oral glucose tolerance test is used for diagnosis using the Carpenter and Coustan criteria (≥2 abnormal values of 95, 180, 155, 140 mg/dL at 0, 1, 2, and 3 h). The current prevalence of GDM in the institution is approximately 15% to 20% of pregnant women.

After diagnosis, nutritional counseling and knowledge on behavioral modification are provided by certified diabetes educators. A glucometer is encouraged and offered for self-monitoring blood glucose (SMBG), but its use is based on women’s preference. FPG or 2-hour PPG, or both, are used for evaluation of glycemic control during follow-up. Glycemic targets are set at FPG <95 mg/dL and 2-hour PPG <120 mg/dL in >80% of the total SMBG test results.

If glycemic targets are not met at any time during pregnancy, repeat nutritional and behavioral counseling is offered. The women are reevaluated every 1 to 2 weeks. If adequate glycemic control is still not achieved within 4 weeks, pharmacological treatment will be initiated. In addition to insulin therapy, metformin will be offered as an alternative medication. The decision on choices of pharmacological therapy is based on the physician’s discretion and the woman’s preference.

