**Inclusion criteria**
Aged ≥18 ySingleton pregnancyDiagnosed with gestational diabetes mellitus, according to institutional guidelines (50-g glucose challenge test followed by 100-g oral glucose tolerance test using the Carpenter and Coustan criteria)Do not achieve glycemic target after nutritional and behavioral counseling (fasting plasma glucose ≥95 mg/dL or 2-hour postprandial glucose ≥120 mg/dL in >20% of total self-monitoring blood glucose test results)

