**Figure 1 figure1:**
[figure not shown]
Study flow diagram.

The rate of achievement of glycemic target within 6 weeks among women with GDM receiving metformin PR and placebo is estimated to be 95% and 70%, respectively, from a pilot data collection. At 95% confidence and 80% power, at least 40 women with GDM are required in each group, estimating a loss of 20% of the participants.

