### Data Collection and Management

Data will be collected at enrollment and at every visit. Data will be entered into the electronic case record form, including baseline and obstetric characteristics, such as age, parity, and prepregnancy BMI. GDM diagnosis and management data, such as gestational age at diagnosis, results of the 50-g glucose challenge test and 100-g oral glucose tolerance test, and glycated hemoglobin, will be collected. Glycemic control data, including FPG and 2-hour PPG at every visit, or percentage of abnormal SMBG test results, will also be noted. Furthermore, the time to achieve the glycemic target will be evaluated, as will side effects, such as bloating, nausea, and vomiting.

Data at every time point will be checked for completeness and entered into the electronic case record form using an electronic data capture system. Data range and values will be rechecked by another research assistant. Incomplete and invalid data will be rechecked with those in the case record form or medical record. An audit trail will be used to track and identify all actions performed on the data, ensuring data integrity.

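### The primary outcome joins the fasting and 2-hour limits with *or*, the plan's own target joins them with *and*, and nothing says how the readings are combined, so entry and success can overlap

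*Protocol article*

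**What the plan says.** The protocol article describes glycemic control in four places.

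- **Outcomes (primary outcome):** success within 6 weeks is "defined as FPG <95 mg/dL or 2-hour PPG <120 mg/dL in >80% of total SMBG test results".
- **Introduction:** optimal glycemic control is a fasting value "of <95 mg/dL and 2-h postprandial glucose, 2-h PPG of <120 mg/dL".
- **GDM Diagnosis and Management:** "Glycemic targets are set at FPG <95 mg/dL and 2-hour PPG <120 mg/dL in >80% of the total SMBG test results".
- **Inclusion criteria:** a woman qualifies with "fasting plasma glucose ≥95 mg/dL or 2-hour postprandial glucose ≥120 mg/dL in >20% of total self-monitoring blood glucose test results".

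Three further statements bear on how the outcome is scored. GDM Diagnosis and Management says that "FPG or 2-hour PPG, or both, are used for evaluation of glycemic control during follow-up", and says of the glucometer, "but its use is based on women’s preference". Data Collection and Management records glycemic data "including FPG and 2-hour PPG at every visit, or percentage of abnormal SMBG test results", and Safety Management offers the same alternative.

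The sample size paragraph after Figure 1 says that the success rate in women "receiving metformin PR and placebo is estimated to be 95% and 70%, respectively, from a pilot data collection". It does not say which definition of success produced those rates.

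**The concern.** One term, optimal glycemic control, has two definitions, and the one that differs is the primary endpoint. The entry criterion is the negation of the *and* target, apart from the case of exactly 80% in range. It is not the negation of the *or* outcome. On the literal per-measure reading, women whose problem is confined to fasting values, or to 2-hour values, are enrolled as uncontrolled and already meet the success definition.

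Such women would add successes to both arms that owe nothing to treatment. The difference between arms would shrink, the reported rate would not be the rate of reaching the plan's own target, and time to control would contain events at time zero. Even if nobody intends this reading, two people scoring the same readings could reach different results on the primary outcome.

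**Working it through.** **1. Entry against success, by pattern.** Take F as the fasting value and P as the 2-hour value, each constant for simplicity. Entry is F ≥95 or P ≥120. Its negation is F <95 and P <120.

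| F / P (mg/dL) | Eligible | Success with *or* | Success with *and* |
|---|---|---|---|
| 90 / 110 | no | yes | yes |
| 90 / 130 | yes | yes | no |
| 100 / 110 | yes | yes | no |
| 100 / 130 | yes | no | no |

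With *or*, two of the three eligible patterns are successes on the day of enrollment. With *and*, none is.

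**2. The same check on shares of SMBG readings.** Assume 7 fasting and 21 two-hour readings; the documents give no counts. All 7 fasting readings are high and no 2-hour reading is.

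- Entry: 7/28 = 25% abnormal, above 20%, so she is eligible.
- Success per measure with *or*: 21/21 = 100% of 2-hour readings in range, above 80%, so she is a success.
- Success with all readings pooled, each against its own limit: 21/28 = 75% in range, so she is not a success.

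The overlap therefore depends on how the share is formed, which the outcome leaves open.

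**3. Why swapping one word is not enough.** Keep the same 28 readings, now with 5 of 7 fasting readings high and all 2-hour readings in range. Pooled, 23/28 = 82.1% are in range, which is a success. Requiring more than 80% for each measure, fasting is 2/7 = 28.6%, which is a failure. The word *and* alone does not choose between these, so the denominator must be stated.

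**4. The plan's own sample size.** Inputs from the plan: 95% and 70%, 80% power, 95% confidence (taken as two-sided 5%), 20% loss. With unpooled variance,

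n = (1.96 + 0.842)² × (0.95×0.05 + 0.70×0.30) / 0.25² = 32.3 per arm.

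Allowing for loss, 32.3/0.8 = 40.4, and 33 × 1.2 = 39.6, or 40. The stated 40 per group is reproduced to within rounding and is not disputed here.

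**5. Illustration of dilution.** Let s be the share of enrolled women who already succeed under *or* and stay successes in both arms. The documents do not give s. Suppose that 95% and 70% hold in the remaining women. The rates become s + (1−s)×0.95 and s + (1−s)×0.70, and the difference is (1−s) × 25 points. Power is the exact power of the two-sided Pearson chi-square test, at 32 per arm (40 less 20%) and at 40 per arm (no loss).

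| s | Metformin PR | Placebo | Difference (points) | Power, 32 per arm | Power, 40 per arm |
|---|---|---|---|---|---|
| 0 | 95% | 70% | 25 | 81% | 89% |
| 30% | 96.5% | 79% | 17.5 | 64% | 74% |
| 50% | 97.5% | 85% | 12.5 | 46% | 58% |

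If the pilot rates were scored with the *or* rule, 95% and 70% already include such women. The first row then applies and nothing is lost against the plan.

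**The case against.** The strongest reply is that the outcome was never meant per measure. Each SMBG reading is either fasting or 2-hour, and both the outcome and the entry criterion refer to a share of total results. The *or* can therefore mean that each reading is held to its own limit and all are pooled. Entry and success are then complementary except at exactly 80%, and the overlap is gone. This is a fair reading, but the outcome does not state it, and the Introduction and management section use a different conjunction for the same target.

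A second reply is that *or* means whichever measure was taken, since the management section allows either or both. That narrows the overlap where a woman has one and the same measure throughout. It does not remove it: a woman enrolled on high 2-hour values could still be scored on fasting values alone.

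A reader might go further and infer that the trial is underpowered, or that a known part of the enrolled women are already successes. The documents support neither. The share s is not given, and the rule behind the pilot rates is not stated. Nor is there reason to infer bias in favor of metformin PR, since baseline successes would be expected in both arms of a randomized, blinded trial. The likely harm is dilution.

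A reader might also infer that women will be scored by different methods because glucometer use is optional. That is weaker. The outcome is tied to SMBG results, the entry criterion already presupposes them, the optional use describes institutional care, and the two other sections concern data collection and safety monitoring. It remains a query only.

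**Conclusion.** The wording conflict is certain: the primary outcome uses *or* where the Introduction and the management section use *and*, and the entry criterion mirrors the *and* rule. The overlap between eligibility and success is conditional. It follows from the literal per-measure reading and is absent under pooled scoring, and the article fixes neither. The primary outcome as worded therefore cannot be scored in one way only, and time to control inherits the problem.

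The effect on the result cannot be sized from the documents. The illustrated fall in power assumes a value of s, assumes that those women succeed in both arms, and assumes that the pilot rates describe only the other women. The sample size of 40 per group is not shown to be wrong. The point should still be settled before unblinding, because it concerns the definition of the primary endpoint.

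**What to change.** - Reword the primary outcome to match the plan's own target: fasting readings judged against <95 mg/dL, 2-hour readings against <120 mg/dL, and success when more than 80% of all readings are in range. State that this is the complement of the entry criterion, and assign the case of exactly 80% to one side.
- Apply the same rule to time to glycemic control.
- State which rule produced the pilot 95% and 70%. If it differed from the reworded outcome, re-check the sample size inputs.
- Confirm that every participant is scored from SMBG, or state the single method used for those without it.
- Make the change while treatment codes are closed, date it, and update the registry record.

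The cost is a short amendment, a registry update and a check of the pilot data. If pooled scoring was always intended, this is a clarification and not a change of endpoint. The article reports 24 women recruited (dated June 2025 in Results and October 2025 in the Abstract). How many are enrolled now is unknown, so their outcomes should be scored by the reworded rule without reference to allocation.

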**Figure 1 figure1:**
[figure not shown]
Study flow diagram.

The rate of achievement of glycemic target within 6 weeks among women with GDM receiving metformin PR and placebo is estimated to be 95% and 70%, respectively, from a pilot data collection. At 95% confidence and 80% power, at least 40 women with GDM are required in each group, estimating a loss of 20% of the participants.

### Assignment of Interventions

#### Randomization

Participants will be allocated to receive either metformin PR or a placebo by simple randomization. Central randomization will be used to minimize the risk of bias. The investigator will contact an independent individual to obtain the randomization list at the time of enrollment of each participant.

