**Methods:**

A randomized, double-blind, placebo-controlled clinical trial will be conducted among 80 pregnant women diagnosed with GDM who had inadequate glycemic control at a university hospital in Thailand. The women will be randomized into 2 equal groups, receiving either metformin PR or a placebo in addition to nutritional therapy and behavioral modification. Dosage adjustment will be made every 2 weeks. If the glycemic target is not achieved within 6 weeks, insulin therapy will be initiated. All the participants and the investigators are blinded to the treatment provided. The primary outcome is the rate of achievement of glycemic control, and secondary outcomes are time to achieve glycemic control, rate of insulin therapy, and factors associated with the success of metformin PR use.

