Our hypothesis is that metformin PR is effective in GDM treatment in terms of the rate of adequate glycemic control and time to achieve glycemic target compared to nutritional therapy. Therefore, the primary objective of this study is to compare the rate of optimal glycemic control within 6 weeks between women with GDM who receive metformin PR and women who receive a placebo, in addition to standard nutritional therapy. The secondary objectives are to compare the time required to achieve optimal glycemic control and the rate of insulin therapy between the 2 groups, and to determine factors associated with the success of metformin PR treatment, such as prepregnancy BMI, degree of abnormalities of test results at the time of diagnosis, GDM risk factors, and other baseline characteristics.

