## Methods

### Study Design

The study is designed as a randomized, double-blind, placebo-controlled trial and registered at the Thai Clinical Trial Registry (TCTR20250525007). Eligible participants will be randomly assigned in a 1:1 ratio to receive either metformin PR or a placebo. Each participant will be followed up every 2 weeks for glycemic control evaluation and dosage adjustment for 6 weeks.

According to the institutional practice guidelines, every woman with GDM will receive counseling by certified diabetes educator nurses and will be scheduled for follow-up every 2 weeks for glycemic control evaluation. If the glycemic target is not achieved after 6 weeks of intensive nutritional therapy, additional pharmacological treatment will be initiated. Therefore, this study will evaluate the primary outcome of glycemic control at 6 weeks after randomization.

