### Statistical Methods

Descriptive statistics, including number, percentage, mean, and SD, will be used to describe variables as appropriate. Comparisons of variables between groups will be made using the 2-tailed Student *t* test for continuous variables, such as age, BMI, and gestational age, or the chi-square test for categorical variables, such as parity and GDM risk factors. Comparison of rates of achievement of optimal glycemic control between groups will be performed using the chi-square test. Relative risks and 95% CIs will be evaluated. Time to achieve glycemic control will be compared between groups, using the Student *t* test or Mann-Whitney *U* test, depending on the distribution of the variables. Kaplan Meier curves will be used to estimate the survival curve of time to achieve glycemic control after treatment, and the log-rank test will be used to compare the survival curves between treatment and control groups. Rates of insulin therapy and side effects will be compared using appropriate statistical tests. Missing values will be handled using multiple imputation methods, as appropriate. Subgroup analysis by BMI categories, parity, or GDM risks will be performed as appropriate. All analyses will be performed on an intention-to-treat basis. A *P* value of <.05 is considered to indicate statistical significance.

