## Results

The study was funded in May 2025, when recruitment started. Women with GDM who had inadequate glycemic control by nutritional therapy were assessed for eligibility. As of June 2025, 24 women with GDM agreed to participate and follow-ups were scheduled. Recruitment will continue until 80 participants are included, which is expected to occur by September 2026. The study is projected to be completed in October 2026. The results are expected to be published in 2027.

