### Strengths and Limitations

The strengths of this study include its randomized, double-blind, placebo-controlled trial design. The diagnosis of GDM follows a uniform institutional guideline. Nutritional and behavioral modifications counseling is provided by well-trained, certified diabetes educator nurses. The main outcome of glycemic control is objectively measured.

Some limitations include that the duration of the intervention and follow-up to evaluate the primary outcome of glycemic control within 6 weeks might not fully capture the long-term effects or improvements after metformin PR treatment. A longer follow-up period is needed to determine whether a higher dose of metformin PR or insulin will be required to achieve adequate glycemic control as pregnancy progresses. In addition, the actual dietary and behavioral practice varies among participants and cannot be accurately measured, which could affect the outcomes. Moreover, the study does not provide a head-to-head comparison between different formulations of metformin, that is, IR versus PR.

The study is not primarily designed to determine if the use of metformin PR improves the pregnancy outcomes, as the study ends at 6 weeks after initiation of the treatment, and further management will vary according to the status of the women and physicians’ discretion. Further well-designed studies on the improvement of GDM-related maternal and neonatal outcomes, such as preeclampsia, large-for-gestational-age infants, and macrosomia, with metformin therapy should be conducted to provide additional evidence on metformin benefits and help aid clinicians’ decisions.

The study is planned to be a pilot randomized clinical trial, and the sample size was calculated based only on the primary objective of comparing glycemic control between the 2 groups and did not take into account for some related factors, such as BMI or gestational age. However, this issue should be considered when designing larger definitive studies in the future. Acknowledging these limitations is essential for interpreting the results and refining future research.

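### Simple randomization with enrolment stopped at 80 will probably not give the equal arms of 40 that the protocol states; the cost is small but blocking is nearly free, and collected baseline data go unused in the stated primary comparison

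*Protocol article*

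**What the plan says.** Four statements in the protocol article bear on arm size.

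- Abstract, Methods: "The women will be randomized into 2 equal groups, receiving either metformin PR or a placebo".
- Methods, Study Design: "Eligible participants will be randomly assigned in a 1:1 ratio to receive either metformin PR or a placebo".
- Sample-size paragraph (after Figure 1, under Outcomes): at least 40 women per arm, from success rates of 95% and 70%, 80% power and a 20% loss.
- Assignment of Interventions, Randomization: "Participants will be allocated to receive either metformin PR or a placebo by simple randomization". Allocation is central, through an independent individual. No blocks, strata or minimization are stated.

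The Results section fixes the total: "Recruitment will continue until 80 participants are included".

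On the analysis, Statistical Methods states: "Comparison of rates of achievement of optimal glycemic control between groups will be performed using the chi-square test". Relative risks with confidence intervals accompany it. BMI, parity and GDM risks appear only as possible subgroups. The Introduction lists candidate factors for success of metformin PR, "such as prepregnancy BMI, degree of abnormalities of test results at the time of diagnosis, GDM risk factors, and other baseline characteristics", and Data Collection and Management records BMI, glucose tolerance results and glycated hemoglobin. Strengths and Limitations says that the sample size "did not take into account for some related factors, such as BMI or gestational age".

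**The concern.** With the total fixed at 80, a minimum of 40 per arm can be met only by an exact 40:40 split. Simple randomization makes the arm sizes random, so the allocation method does not deliver what the Abstract and the sample-size paragraph state.

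The design also has little power to spare. The 40 per arm is 32 evaluable women inflated for loss, so at the planned loss any arm below 40 is expected to fall short of 32. For example, 36 × 0.8 = 28.8.

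The second part concerns precision. The trial collects baseline values that may predict success, but neither the allocation nor the stated primary comparison uses them. A chance imbalance in a factor that does predict success would pass into the unadjusted estimate.

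**Working it through.** **Inputs from the protocol.** Success 95% v 70%; 80% power; 20% loss; 40 per arm; total 80; simple 1:1 allocation; chi-square test. A two-sided 5% level is assumed from the 95% confidence and the P<.05 criterion.

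**1. The plan's own figure.** Arcsine formula: n = 2(z₀.₉₇₅ + z₀.₈₀)² / h², with h = 2·arcsin√0.95 − 2·arcsin√0.70 = 0.708. So n = 2 × (1.960 + 0.842)² / 0.708² ≈ 31.3, rounded up to 32, and 32/0.8 = 40. The stated 40 per arm reproduces.

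**2. Arm sizes.** The number on metformin is Binomial(80, 0.5).

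| Event | Probability |
|---|---|
| exactly 40:40 | 8.9% |
| one arm below 40 | 91% |
| 35:45 or worse | 31% |
| 32:48 or worse | 9.3% |
| 30:50 or worse | 3.3% |

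**3. Effect on power.** Exact enumeration of the uncorrected chi-square at 95% v 70%. The 64 evaluable women are 80 × 0.8, with loss assumed unrelated to arm.

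| Evaluable split (metformin:placebo) | Power |
|---|---|
| 32:32 | 80.6% |
| average over Binomial(64, 0.5) | 79.4% |
| 24:40 | 73.8% |
| 40:24 | 81.9% |

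The average loss is 80.6 − 79.4 = 1.2 points. The effect is not symmetric: the placebo rate carries the larger variance (0.70 × 0.30 = 0.21 v 0.95 × 0.05 = 0.0475), so a larger placebo arm costs power and a moderately larger metformin arm does not. The chance of 24 or fewer on metformin out of 64 is 3.0%. With all 80 evaluable, power is 88.8% at 40:40 and averages 88.0%.

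**4. Covariate imbalance.** The protocol gives no prevalences. For a binary factor with assumed prevalence 40% and 40 per arm, the SD of the between-arm difference is √(0.4 × 0.6 × 2/40) = 0.11, or 11 points. At assumed prevalences of 30% to 50%, the chance of a gap of 15 points or more is 18% to 22%.

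**5. What using a covariate could gain.** Simulation with 64 evaluable women, one binary factor, assumed prevalence 50% and 6,000 runs per setting:

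| Assumed odds ratio | Simple allocation, chi-square | Stratified allocation, Mantel-Haenszel |
|---|---|---|
| 2 or 4 | 79% | 81% |
| 8 | 80% | 84% |

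Keeping simple allocation and changing only the analysis gives 78.9% to 80.5% at an odds ratio of 4, and 80.3% to 83.2% at 8. Across the settings run, type I error of the unadjusted test under simple allocation was 4.8% to 5.8%.

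**6. Events available.** Expected failures among 80: 40 × 0.05 + 40 × 0.30 = 2 + 12 = 14. Among 64: 32 × 0.05 + 32 × 0.30 = 1.6 + 9.6 = 11.2.

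**7. Effect of changing now.** The protocol reports 24 women who agreed to take part, leaving 80 − 24 = 56. If all 24 were allocated by simple randomization, the SD of the difference in arm sizes falls from √80 = 8.9 to about √24 = 4.9 when the other 56 are blocked.

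**The case against.** The strongest reply is that nothing here is invalid. Simple randomization and an unadjusted chi-square are both sound, type I error stays near 5%, and the average power loss is about one point. That stands.

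Equal groups may also be loose wording for a 1:1 ratio, which simple randomization meets in expectation. That is plausible for the Abstract. It does not explain a minimum of 40 per arm within a fixed total of 80.

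Four stronger readings are tempting, and the documents do not support them.

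- *Unequal arms seriously weaken the trial.* The 73.8% at 24:40 is the unfavorable direction and lies at the edge of what is likely. The mirror split has more power than equal arms.
- *The plan ignores known prognostic factors.* The Introduction lists BMI and test severity as factors whose association with success is still to be determined. The limitation about related factors concerns sample size only. No passage gives their strength, so the size of any distortion is unknown.
- *An adjusted analysis is missing.* One may stand in a statistical analysis plan that is not shown. What can be said is that the comparison stated here does not use the baseline data.
- *The between-group tests of age, BMI and similar variables are an error.* They change no result, and nothing says that adjustment will follow from them.

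It is also fair that a mid-trial change cannot repair earlier imbalance, and that a regression with about 2 failures in the metformin arm is fragile. Both points limit the remedy.

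**Conclusion.** The point holds as an internal inconsistency with a modest statistical cost. The stated allocation method, with the total fixed at 80, meets the stated 40 per arm with probability 8.9% and gives 35:45 or worse with probability 31%. These figures need only the 1:1 ratio and the total.

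The cost is in precision, not validity: about 1.2 points of power on average at 64 evaluable women, and about 7 points (80.6% to 73.8%) in an unfavorable split of roughly 3% probability or less. This rests on the protocol's 95% and 70% and on loss unrelated to arm.

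The unused baseline data are a smaller matter. The gain is about 2 to 4 points of power for assumed odds ratios of 2 to 8, in a simulation of stratified allocation with stratified analysis. It is somewhat less from adjustment alone. The odds ratios and prevalence are assumptions. The change is worth making because it is cheap and still possible; it is not essential to a valid result.

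**What to change.** 1. **Allocation.** By amendment, have the independent person who already issues allocations use permuted blocks of varying, concealed size for all women not yet allocated. Varying sizes matter because the Blinding section provides for unblinding after withdrawal, and a known block size would then help someone guess later assignments. Under blocking, the later women can differ in arm size by at most half the largest block. The number still to be allocated should come from the allocation log, since the Abstract and the Results section date the count of 24 differently.
2. **Wording.** Reconcile the Abstract, Study Design, the sample-size paragraph and Randomization, so that they state one allocation method and say whether 40 per arm is a requirement or an expectation.
3. **Analysis.** Before unblinding, pre-specify a risk difference and relative risk adjusted for at most two collected baseline covariates, for example glycemic control at entry and prepregnancy BMI. Use logistic regression with standardization and a Firth-type correction if the data are sparse. Report this alongside the chi-square.

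**Cost.** An amendment, a new list for the remaining women and a few sentences of analysis text. Blocking cannot undo imbalance among women already allocated. With about 11 to 14 expected failures, the adjusted model cannot grow beyond two covariates and its gain will be modest.
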